### Days of oxygenation

The median time to weaning of oxygenotherapy will be summarized by treatment group.

Time to oxygenation weaning will be compared between groups using Fine & Gray method to take into account competing risk (death).

### Days of Non-invasive ventilation/high-flow oxygen

The median days of non invasive ventilation or high-flow oxygen use during study will be summarized by treatment group. Patients who did not receive non invasive ventilation will have a number of days equal to 0.

Time to non-invasive ventilation/high flow oxygen use will be compared between groups using Fine & Gray method to take into account competing risk (death).

### Days of invasive ventilation /ECMO

The median days of invasive ventilation or ECMO use during study will be summarized by treatment group.

Time to invasive ventilation/ECMO will be compared between groups using Fine & Gray method to take into account competing risk (death).

### Days of hospitalization

The median duration of initial hospitalization will be summarized by treatment group.

Time to discharge will be compared between groups using Fine & Gray method to take into account competing risk (death).

### Transfer in ICU

ICU transfer rate will be summarized by treatment group at day 8, day 15 and day 29.

Time to ICU transfer will be compared between groups using Fine & Gray method to take into account competing risk (death).

### Death

Mortality rate will be summarized by treatment group at day 15, day 29 and day 60.

Time data’s will be analyzed using a stratified log-rank test by treatment groups. Differences will be summarized with Kaplan-Meier curves and 95% confidence bounds.

The median time to event and 95% CI in each treatment group will be summarized and log rank test will be performed. Differences in time-to-event endpoints by treatment arm will be summarized with Kaplan-Meier curves. Number at risk, hazard ratio and log rank p-values will be presented on the figures.

Hazard ratio and 95%CI will be performed using Cox proportional hazards model.

28-day mortality may be summarized according to proportions by category and/or odds ratios with confidence intervals.

### Safety Analyses

Safety endpoints include death through Day 60, SAEs and Grade 3 and 4 AEs.

Each AE will be counted once for a given subject and graded by severity and relationship to COVID-19 or study intervention. AEs will be coded using the current version of the Medical Dictionary for Regulatory Activities (MedDRA). AEs will be presented by system organ class, duration (in days). Adverse events leading to premature discontinuation from the study intervention and serious treatment-emergent AEs will be presented either in a table or a listing.

## Covariates and Subgroups

Subgroup analyses for the main efficacy outcomes will evaluate the treatment effect across the following subgroups:

• Duration of symptoms prior to enrollment

o <= 6 days; 7 to 10 days, 11 to 14 days

• COVID serology at randomization

o Positive

o Negative

• Oxygene Flow at randomization

o < 4l/min

o >=4 l/min

• Immunodepressive status (Solid tumor, leukemia, lymphoma, metastatic solid tumor, HIV)

o Positive

o Negative

• Comorbidities

o Number of conditions : None; One; Two or more

• Clinical status at baseline (NEWS score):

2-4

o 5-6,

o 7 and more

• Concomitant treatment of COVID if possible

• Concomitant treatment of coexisting conditions

• Age

o < 50

o 50-65

o 65-75

o > 75

or by the median (or quartiles) according to the sample size

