**Dose determination for Phase 2a**

Based on preclinical assessment of the elimination half-life of swine glyco-humanized IgG in non-human primates (baboon), it was hypothesized for the first cohort of Phase 2a of POLYCOR (low dose at 0.5mg/kg) that 2 doses 4 days apart (Day 1 and Day 5) would be necessary to obtain serum neutralizing antibodies titers maintained for 10 days. This period of 10 days was initially considered as the duration of productive SARS-CoV-2 infection during covid-19. Today, the first data from clinical trials evaluating the benefit of polyclonal anti-SARS-CoV-2 immunoglobulins (such as in Hueso et al, Blood, 2020 in immunocompromised patients) indicated that neutralizing antibodies result in clinical benefits within a few days (as low as 3 days). In addition, preliminary data of XAV-19 PK in the first 3 patients who received the low-dose of 0,5 mg/kg during the first cohort of POLYCOR Phase 2a, suggest that effective concentrations will be obtained for more than a week with a single higher dose, without need for a second dose administration. This has been confirmed with preliminary PK data in the first 4 patients who received a single dose of Xav-19 of 2mg/kg in the second part of the phase 2a. Concentrations were above the effective target concentration of neutralizing specific antibodies (10,000 ng/ml), with a mean peak post-infusion concentration around 50,000 ng/ml, and concentrations maintained >15 days above target. Maintaining a pharmacodynamic effect of neutralizing antibodies over more than a week is considered as an appropriate period of time to improve recovery and diminish worsening.

Dose levels selected in the First In Human assessment of XAV-19 are based on 3 datasets:

1) Assessment of the higher acceptable dose: Available clinical experience (EUDRACT 2019-000917-35) indicate than swine glyco-humanized antibodies are well tolerated at doses so far tested up to 40mg/Kg (cumulative dose after 5 daily administrations of 8 mg/Kg). Therefore, in this First In Human trial with XAV-19, the cumulative dose is proposed to be inferior to this so far tested upper limit.

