### Non-inclusion criteria

1. Evidence of multiorgan failure (severe COVID-19)
2. Mechanically ventilated (including ECMO)
3. Receipt of immunoglobulins or any blood products in the past 30 days
4. Psychiatric or cognitive illness or recreational drug/alcohol use that in the opinion of the investigator, would affect subject safety and/or compliance
5. End-stage renal disease (eGFR < 15 ml/min/1,73 m^2^)
6. Child-Pugh C stage liver cirrhosis
7. Decompensated cardiac insufficiency
8. Known allergy, hypersensitivity, or intolerance to the study drug, or to any of its components
9. Females of childbearing potential without contraceptive method, or with positive pregnancy test, breastfeeding, or planning to become pregnant during the study period
10. Current documented and uncontrolled bacterial infection.
11. Prior severe (grade 3) allergic reactions to plasma transfusion
12. Patient participating in another interventional clinical trial
13. Life expectancy estimated to be less than 6 months
14. Patient under guardianship or trusteeship
15. Patient already included
16. Prior hospitalisation in intensive care unit for the current covid-19 episode

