**Table 1. Baseline patient’s characteristics**

| **Characteristics** | **Xav19 + Soc** (N=) | **Placebo + Soc** (N=) |
| --- | --- | --- |
| **Baseline demographics and medical history** |  |  |
| **Age** (in years) |  |  |
| Mean (SD) |  |  |
| Category N (%) |  |  |
| <=50 |  |  |
| > 50-65 |  |  |
| > 65-75  > 75 |  |  |
| **Sex (N (%))** |  |  |
| Women |  |  |
| **Height** mean (SD) |  |  |
| **Weight** mean (SD) |  |  |
| **BMI**  Mean (SD)  Category N (%)  <30  30-34  35-40  >40 |  |  |
| **Medical history** |  |  |
| Hypertension  Other chronic cardiovascular disease |  |  |
| Diabetes |  |  |
| COPD  Other chronic lung disease, including asthma |  |  |
| Chronic kidney disease, including dialysis  Cancer  Solid organ transplant  HIV infection  Other immunosuppressive condition, based on investigator’s assessment |  |  |
|  |  |  |
| **Duration of symptoms before enrollment** |  |  |
| Mean (SD) |  |  |
| ≤ 6 days (%) |  |  |
| 7-10 days |  |  |
| 11-14 days  **Concomitant treatment** |  |  |
|  |  |  |
| **NEWS score** N (%)  2-4 |  |  |
| 5-6 |  |  |
| 7 and more  **SpO2 Mean ( SD)**  **O2 supplement**  < 4L/min  ≥4L/min  Variant’s type  COVID serology if possible |  |  |

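### The SAP's immunodepressive-status subgroup omits solid organ transplant and other immunosuppressive conditions that its own Table 1 records, so patients with only one of these are coded Negative

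*Combined protocol and SAP*

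**What the plan says.** SAP section 5.3 introduces its list with "Subgroup analyses for the main efficacy outcomes will evaluate the treatment effect across the following subgroups". One entry is "Immunodepressive status (Solid tumor, leukemia, lymphoma, metastatic solid tumor, HIV", with levels Positive and Negative. The list carries no wording such as 'for example', no 'other' category and no third level.

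SAP Table 1 (baseline characteristics) has a single row for cancer, then "Solid organ transplant", "HIV infection" and "Other immunosuppressive condition, based on investigator’s assessment". Transplant stands between cancer and HIV, and the word 'Other' in the last row suggests that the SAP counts these neighbouring rows as immunosuppressive.

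The Phase 2b exclusion criteria (protocol 5.2.2, repeated in SAP 2.2) do not mention transplant or immunosuppression. The nearest is "Receipt of immunoglobulins or any blood products in the past 30 days", which concerns a recent treatment and not the condition. No other section adds the two items to the subgroup.

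**The concern.** The SAP holds two lists for one concept, and they do not match. Read as written, a graft recipient with no listed condition is analysed as not immunodepressed. So is a patient whom the investigator has recorded as immunosuppressed for another reason. Any patient with a solid tumour is analysed as immunodepressed. The variable is in effect cancer or HIV, whatever its label says.

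The question has some interest for this product. The introductions to the protocol and the SAP motivate passive antibody by a suboptimal early antibody response of the patient's own. At stake are a Negative estimate that contains immunosuppressed patients and a Positive group that leaves out patients whose data are already planned.

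**Working it through.** **Comparison of the two lists**

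| Condition | SAP Table 1 | SAP 5.3 subgroup |
|---|---|---|
| Cancer | one row | solid, metastatic solid, leukaemia, lymphoma named |
| HIV | own row | named |
| Solid organ transplant | own row | absent |
| Other immunosuppressive condition | own row, investigator's assessment | absent |

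Two rows are missing from the subgroup. The SAP does not say how patients with only these conditions are coded; Negative follows from a closed list with two levels. A transplant recipient who also has a listed condition is still Positive.

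**The plan's own figure.** SAP 2.7 gives 398 patients for 20% versus 10%, two-sided 5%, at least 80% power. With pooled variance under the null hypothesis and no continuity correction:

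n per arm = [1.960·√(2·0.15·0.85) + 0.842·√(0.20·0.80 + 0.10·0.90)]² / 0.10² = 199, so 398 in total, with power 80.0%. This reproduces, and the subgroup definition does not enter it.

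**Size of the misclassification.** All prevalences here are assumptions: omitted condition only, 3% to 6% of 398 (12 to 24 patients); listed condition, 8% to 10% (32 to 40). The low omitted figure is paired with the high listed figure, and the reverse.

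- Share of immunosuppressed patients missed = omitted / (omitted + listed): 12/52 = 23%; 24/56 = 43%.
- Share of the Negative group misplaced, w = omitted / (398 − listed): 12/358 = 3.4%; 24/366 = 6.6%.

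**Effect on the contrast.** Suppose omitted patients respond as listed ones do. Let D1 be the risk difference in immunosuppressed patients and D0 that in the others. The Positive estimate still targets D1, because no omitted patient is in it. The Negative estimate targets w·D1 + (1 − w)·D0. The expected contrast is therefore (1 − w)(D1 − D0). With D1 = 20 points and D0 = 8 points, both assumed, a true contrast of 12 points reads 12 × 0.966 = 11.6 or 12 × 0.934 = 11.2. Under wider assumptions (5% to 10% listed, 2% to 10% omitted), 2% to 11% of the Negative group is misplaced and the contrast reads 10.7 to 11.7.

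**Effect on precision in the Positive group.** With equal arms of m patients and the planning rates of 20% versus 10%, the half-width of the 95% interval is 1.96·√[(0.16 + 0.09)/m].

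| Positive group | m per arm | Half-width (points) |
|---|---|---|
| 32, current list | 16 | 24.5 |
| 40, current list | 20 | 21.9 |
| 52, both items added (40 + 12) | 26 | 19.2 |
| 56, both items added (32 + 24) | 28 | 18.5 |

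The other two pairings, 32 + 12 = 44 and 40 + 24 = 64, give 20.9 and 17.3 points.

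**The case against.** The strongest reply is that this is one of nine subgroups and none of them is confirmatory. SAP 3.1 applies no multiplicity correction and treats all secondary objectives as exploratory. Even after the change, the half-width in the Positive group is well above the planned 10-point effect. Section 5.3 also has a subgroup by COVID serology at randomization, which is closer to the question of whether a patient has antibody of their own, and the Phase 2b schedule includes that serology at screening. A list of named diagnoses is reproducible, whereas an investigator's assessment with no stated criteria is not.

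Most of this stands, and it limits the point to a cheap improvement. It does not remove the mismatch. Serology is a different variable, Table 1 lists it only where possible, and the comorbidity subgroup merely counts conditions.

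A reader might also infer three stronger things that the documents do not support.

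- *That the misplacement could reverse the subgroup contrast.* If omitted and listed patients respond alike, the factor (1 − w) is positive, so the expected contrast shrinks but keeps its sign. Reversal would need the two kinds of patient to respond differently, and nothing in the documents suggests that.
- *That a pre-specified interaction test is damaged.* Section 5.3 names no interaction test.
- *That the protocol expects the greatest benefit in immunocompromised patients.* Protocol 1.3 cites data from such patients, saying they "indicated that neutralizing antibodies result in clinical benefits within a few days". It uses them to argue how soon benefit appears and why one dose may suffice, and it does not compare patient groups.

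**Conclusion.** The point holds as a labelling and classification fault in a supportive subgroup. The text alone establishes that two immunosuppression items planned for Table 1 are absent from the definition, and that eligible patients with only these conditions fall into Negative. The size rests wholly on assumed prevalences. The 23% to 43% of immunosuppressed patients missed should not be read as contamination of the comparator, which is about 3% to 7%. The main costs are the misleading label and the patients lost from a small group; the dilution is minor. The primary test, the sample size and the trial's objectives do not change. The correction is worth making but is not needed for the validity of the trial.

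**What to change.** Amend SAP 5.3 before the unblinding described in SAP 2.6:

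- Define Positive as any of cancer (solid or haematological), HIV infection, solid organ transplant, or other immunosuppressive condition as recorded for Table 1. Define Negative as none of these.
- Align the single cancer row of Table 1 with the cancer types named in 5.3, so that both rest on the same variable.
- Add a sensitivity analysis that leaves out the investigator-judged item.
- If the narrower list is intended, keep it, give the reason, and rename the subgroup 'Cancer or HIV'.

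The cost is a few lines of SAP text, one recoded variable and one extra subgroup run. The items are already planned for Table 1, so no new data are needed. The one drawback is that the last item depends on investigator judgement, which the sensitivity analysis addresses. The timing matters: deciding after unblinding which patients count as immunodepressed would be open to the charge of being driven by the results.

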## Missing Data

All attempts will be made to collect all data per protocol. Any data point that appears to be erroneous or inexplicable based on clinical judgment will be investigated as a possible outlier. If data points are identified as outliers, sensitivity analyses may be performed to examine the impact of including or excluding the outliers. Any substantive differences in these analyses will be reported.

### Primary and key secondary outcome

Subjects who withdrew their consent before Day 15 will be imputed using multiple imputation.

Subjects who are discharged but are subsequently re-admitted prior to Day 15 without a reported 8-point ordinal scale, their ordinal score will be imputed at 7, which is the highest value for a hospitalized subject.

For subjects who are discharged, if no visit is done at day 15 +/ 2 days then the reported ordinal score will be imputed at 2 (highest level for ambulatory patients).

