## Rules for discontinuing subject participation

### Criteria in respect of early withdrawal of a subject from the study

Withdrawals from the study can only be effective after confirmation by the investigator and the sponsor. These withdrawals are always definitive

Patients can withdraw from participation in this study at any time, for any reason, specified or unspecified, and without prejudice.

Criteria in respect of early withdrawal of a subject from the study are the following:

- Withdrawal of informed consent (subject’s decision to withdraw for any reason). All data gathered before their withdrawal will be kept for analysis
- Investigator’s decision to stop the study in the patient’s best interest. Patients who stop prematurely or definitively the study treatment will be kept in the study for follow-up
- Subjects who have grade 4 reaction secondary to first XAV-19 administration and/or develop serum sickness disease, serious allergic reaction such as anaphylactic shock, severe hypotension, tachycardia or Quincke’s edema following first XAV-19 administration will discontinue study treatment but will be kept in the study to perform the required study-related follow-up and procedures
- For the phase 2a, subjects who discontinue prior to the Day 8 in phase 2a will be replaced, in order to obtain the required number of evaluable subjects in each group (8 patients). There will be no replacement of discontinued patients in phase 2b.
- Termination of the study by the Sponsor

Stopping rules:

| **Parameter** | **Value** |
| --- | --- |
| Adverse events | Grade 4 reaction secondary to first XAV-19 administration and/or develop serum sickness disease, serious allergic reaction such as anaphylactic shock, severe hypotension, tachycardia or Quincke’s edema |
| **Vital signs** |  |
| - Bradycardia | - <50 beats/min or ECG abnormalities |
| - Tachycardia | - >130 beats/min or ventricular dysrhythmias |
| Supine systolic blood pressure increase | >200 mmHg or headache or clinical signs |
| Supine diastolic blood pressure increase | >120 mmHg or headache or clinical signs |
| Supine systolic blood pressure decrease | <70 mmHg or symptomatic |

Every effort should be made to keep the patients in the trial, if possible, on treatment, or at least post-treatment discontinuation to collect important trial data.

For the data processing procedures in respect of subjects withdrawn early from the study, refer to the statistical section.

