## Sample size calculation

In the phase 2b, about 398 randomized patients, 199 patients in each group, will be included.

Assuming a true treatment difference in clinical failure rate of 10% for XAV-19 added to SoC therapy compared to placebo added to SoC therapy where a rate of 20% is expected, a sample size of 398 participants provides at least 80% power that the primary analysis will be statistically significant at the two-sided 5% significance level.

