# General statistical considerations

## General Principes

### Confidence intervals and p-values

All applicable statistical tests will be 2-sided and will be performed using a 5% significance level.

No correction for multiple comparisons will be applied; all secondary objectives will be considered as exploratory and results were reported with only effect size estimates with their confidence intervals (CIs). All CIs presented will be 95%CI and 2-sided.

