## Protocol deviations

The following protocol deviations are pre-defined as major protocol violations with a direct bearing on primary outcome:

- Patients who did not respect treatment scheduled (i.e. for who treatment was not administrated or not entirely administrated)

- Patients who did not received the allocated treatment (treatment cross-over)

- Patients who did not verify all major inclusion criteria and all major non-inclusion criteria

- Patients lost to follow-up before day 15

- Patients who withdrew their consent before day 15

- Patients who had a respiratory failure before treatment administration

Protocol deviations will be identified and classified as major or minor in blind reviews before the database freezing. The number and % of patients with major and minor protocol deviations will be provided by treatment group, with details of the type of deviation. No formal statistical comparison will be done.

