## Population definition

**Intent-to-treat (ITT) Population**: The ITT population will include all randomized patients, regardless of their eligibility and any protocol deviations, according to the treatment group to which they were assigned at randomization.

**Modified Intent-to-treat (mITT) Population**: The mITT population will include the ITT population but will exclude:

1. Patients who did not received treatment for any reason (withdrawn consent or investigator decision due to quick worsening of respiratory status before administration)
2. Patients with legal requirements (i.e. guardianship or trusteeship, < 18 years, no signed consent).

**Per-protocol (PP)**: The PP population will include the mITT population but will exclude:

1. Patients with treatment cross over, defined as receiving the other treatment
2. Patients with withdrawn consent between D1 and D15
3. Patients with major inclusion or non-inclusion criteria violation
4. Patients with major protocol deviations listed in section 3.2

The primary endpoint and the key secondary endpoints will be analysed on the ITT, mITT and the PP population.

The other secondary endpoints will be analysed on the mITT population only.

**Safety population**: The safety population will be included all randomized patients who have received the study treatment or placebo.

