### Respiratory failure or death

Respiratory failure is defined by a requirement of low oxygen delivery device and a flow ≥ 10 L / min with reservoir, or high-flow oxygen devices or noninvasive ventilation, or invasive mechanical ventilation or death after infusion of treatment. This is related to a value of 5, 6, 7, or 8 on the clinical status 8-point ordinal scale.

Respiratory failure will be evaluated between baseline and day 15 (primary objective), between baseline and day 8, and between baseline and day 29 (key secondary objectives).

The primary outcome measures the number of patients who had at least one respiratory failure after baseline (D1 before infusion).

The time to respiratory failure will be defined as the elapsed time (in days) from baseline (on Day 1) to the first day at which a subject reaches any respiratory failure.

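### The imputation and per-protocol rules for patients who leave before Day 15 make no exception for a respiratory failure already observed, and the Day 15 cut-off is also applied to the Day 8 endpoint

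*Combined protocol and SAP*

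**What the plan says.** **Outcome.** SAP section 5.1 (Respiratory failure or death) says: "The primary outcome measures the number of patients who had at least one respiratory failure after baseline (D1 before infusion"). The same event is assessed from baseline to Day 8 and to Day 29 as the key secondary endpoints.

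**Data before withdrawal.** Under withdrawal of consent, protocol section 6.7.1 says: "All data gathered before their withdrawal will be kept for analysis".

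**Imputation.** SAP section 5.4, under the heading for the primary and key secondary outcomes, says: "Subjects who withdrew their consent before Day 15 will be imputed using multiple imputation". Protocol section 7.2.4 has a similar rule for the primary outcome. It sends any patient not followed to Day 15 to multiple imputation, adds a sensitivity analysis on the imputation method, and states that no missing primary data are expected. Neither text refers to events seen before the patient left.

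**Per-protocol set.** SAP section 3.3 excludes "Patients with withdrawn consent between D1 and D15". It also excludes the major deviations of section 3.2, which include "Patients lost to follow-up before day 15" as well as consent withdrawal before that day. Neither exclusion depends on event status.

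**Where the rules apply.** SAP section 3.3 analyses the primary and key secondary endpoints on ITT, mITT and per-protocol. A treated patient who later withdraws stays in ITT and mITT.

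**The concern.** The endpoint asks whether at least one failure occurred by a given day. Once a patient has gone onto high-flow oxygen, non-invasive or invasive ventilation, or a reservoir mask at the qualifying flow, the answer for that day and every later horizon is yes. Later withdrawal cannot change it.

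The rules for leavers look only at when the patient left. Take a patient who starts high-flow oxygen on Day 4 and withdraws consent on Day 9. By definition this is a primary failure. By the wording of SAP section 5.4 it is a case for imputation, and by section 3.3 it leaves the per-protocol set.

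For the Day 8 endpoint the mismatch does not even need an event. A patient who withdraws on Day 10 has a complete Day 8 record, failed or not, yet meets the imputation rule and the per-protocol exclusion.

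At stake is the count of primary events. About 40 are expected on placebo and 20 on XAV-19, so a few reclassified patients would show in the estimate. A rule that leaves this open also allows the handling of known failures to be settled after unblinding.

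**Working it through.** **1. The plan's own figure.** Inputs: "Assuming a true treatment difference in clinical failure rate of 10% for XAV-19 added to SoC therapy" and "where a rate of 20% is expected, a sample size of 398 participants provides at least 80% power" (SAP section 2.7); "All applicable statistical tests will be 2-sided and will be performed using a 5% significance level" (SAP section 3.1); 199 patients per arm.

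n per arm = [1.960 × √(2 × 0.15 × 0.85) + 0.842 × √(0.20 × 0.80 + 0.10 × 0.90)]² / 0.10² = 199, so 398 in total. This matches. Power at 199 per arm is 80.0%, with no allowance for withdrawal. Expected failures: 199 × 0.20 = 39.8 on placebo and 199 × 0.10 = 19.9 on XAV-19.

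**2. The texts side by side.**

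| Patient | Outcome definition | SAP 5.4 as worded | Per-protocol set |
|---|---|---|---|
| Fails Day 4, withdraws consent Day 9 | Failure at Days 8, 15 and 29 | Imputed | Excluded |
| Fails Day 4, lost Day 9 | Failure at Days 8, 15 and 29 | Not named (protocol 7.2.4 would impute the primary outcome) | Excluded |
| Event-free, withdraws consent Day 10 | Day 8 known; Day 15 unknown | Imputed, Day 8 included | Excluded, Day 8 included |

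By contrast, the time-to-event rule in SAP section 5.4 censors only patients who leave before their event. Read literally, the first patient is an event in the time-to-respiratory-failure analysis and an imputed value in the primary analysis.

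**3. Size if the same fraction of failures withdraws in each arm.** The documents give no withdrawal rate and no imputation model, so these are assumptions. Let k placebo failures withdraw before Day 15. The same fraction on XAV-19 is k/2, because half as many failures are expected. Redraw each at the planned arm rate, 0.2 or 0.1.

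- Expected failures lost on placebo: 0.8k
- Expected failures lost on XAV-19: 0.9 × k/2 = 0.45k
- Shrinkage of the difference: (0.8k − 0.45k)/199 = 0.35k/199

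For k = 1, 3 and 5 this is 0.18, 0.53 and 0.88 points of the planned 10.

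Per-protocol with k = 3, removing only these patients: 36.8/196 − 18.4/197.5 = 18.78% − 9.32% = 9.46 points, a loss of 0.54.

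**4. Size if prior failures are unevenly spread.** Assume ten withdrawers per arm. Under the literal rule all ten are imputed at the rate among the other 189. With events kept, only those without a prior event are imputed.

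| Prior failures among withdrawers (placebo, XAV-19) | Difference, literal rule | Difference, events kept |
|---|---|---|
| 5, 0 | 34.8/189 − 19.9/189 = 7.9 points | 9.9 points |
| 0, 5 | 39.8/189 − 14.9/189 = 13.2 points | 10.9 points |
| 5, 5 | 34.8/189 − 14.9/189 = 10.5 points | 10.3 points |

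First row, events kept: (39.8 + 5 × 0.184)/199 − (19.9 + 10 × 0.105)/199 = 20.5% − 10.5% = 9.9 points after rounding. The shift is about 2 points in either direction when prior failures fall in one arm, and small when they are equal in number.

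**The case against.** The strongest reply is that the imputation sentence stands in a section on missing data, and multiple imputation fills only missing values. An outcome settled at the first failure is not missing, and neither is a completed Day 8 status. The SAP's own definition and protocol section 6.7.1 both point to keeping the event, and protocol section 7.2.6 keeps consent withdrawals in its full analysis set. Nothing in the documents says that a recorded failure is overwritten. This stands: a reader might infer that the SAP discards observed events in ITT and mITT, and the documents do not support that as a stated instruction. It is one literal reading of unqualified wording. It remains a plausible reading, because the time-to-event rule in the same section does condition on earlier events and this rule does not.

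A reader might also infer that every early leaver is imputed or excluded everywhere. That is too wide. The SAP's imputation sentence names consent withdrawal only, and exclusion on these grounds affects the per-protocol set only. Nor is this a departure of the SAP from the protocol, since protocol section 7.2.4 is equally unqualified.

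A third tempting inference is that the rule must shrink the treatment effect. Step 4 shows that the direction can reverse, and nothing in the documents shows that consent withdrawal follows deterioration.

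Finally, removing early leavers is an ordinary purpose of a per-protocol set, this is one of three sets, and SAP section 3.1 treats secondary results as exploratory. That limits the consequence. It does not explain removing a patient whose status for the endpoint is already known.

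**Conclusion.** The concern holds as a gap and an inconsistency in the rules. For the per-protocol analyses the loss of observed failures is explicit. For ITT and mITT it is a risk created by wording without an event exception, at odds with the outcome definition and with the retention of pre-withdrawal data. For the Day 8 endpoint the Day 15 cut-off is wrong on its face.

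The likely effect is modest: about 0.2 to 0.9 points of the planned 10 for one to five placebo failures withdrawing, with a proportional number on XAV-19, and about 2 points in either direction in the one-arm scenarios shown. These figures rest on assumed withdrawal numbers and on imputation draws that ignore the recorded failure. If few or no patients fail and then leave before Day 15, the effect is negligible. The rule still merits correction before unblinding, because it governs the primary endpoint and the design has 80.0% power with nothing in reserve.

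**What to change.** - **SAP section 5.4 and protocol section 7.2.4.** State that a patient with respiratory failure or death observed by Day 8, 15 or 29 counts as a failure for that endpoint whatever happens later. Impute only patients whose status is unknown at that endpoint's own horizon.
- **SAP sections 3.2 and 3.3.** Do not exclude a patient from the per-protocol analysis of an endpoint on grounds of withdrawal or loss alone when that patient's status for the endpoint is already known.
- **Consistency.** Check both changes against the outcome definition in SAP section 5.1 and the retention rule in protocol section 6.7.1, so that all of these texts give the same answer for the same patient.

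The cost is a few sentences. No new data are needed and the sample size of 398 is unchanged. The downside is that a few patients who later withdrew stay in the per-protocol set, and that set can differ slightly between the Day 8, Day 15 and Day 29 analyses, so its size should be reported for each.
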